## Abstract

**Background:**

In a previous feasibility study (APROPOS) in a single municipality of the Netherlands, we showed that a locally tailored preconception care (PCC) approach has the potential to positively affect preconceptional lifestyle behaviours. Therefore, we designed a second study (APROPOS-II) to obtain a more robust body of evidence: a larger group of respondents, more municipalities, randomization, and a more comprehensive set of (clinical) outcomes. The aim of this study is to assess the effectiveness and the implementation process of a local PCC-approach on preconceptional lifestyle behaviours, health outcomes and the reach of PCC among prospective parents and healthcare providers.

**Methods:**

This study is an effectiveness-implementation hybrid type 2 trial. This involves a stepped-wedge cluster randomized controlled trial design aiming to include over 2000 future parents from six municipalities in the Netherlands. The intervention has a dual-track approach, focusing on both the uptake of PCC among future parents and the provision of PCC by healthcare providers. The PCC-approach consists of 1) a social marketing strategy directed towards prospective parent(s) and 2) a local care pathway to improve interdisciplinary collaboration. Data will be collected before and after the introduction of the intervention through questionnaires and medical records in each of the participating municipalities. The primary outcome of this study is change in lifestyle behaviours (e.g. folic acid use, smoking and alcohol use). Secondary outcomes are pregnancy outcomes (e.g. miscarriage, preterm birth, gestational diabetes) and the uptake of PCC. Moreover, a process evaluation will be performed, providing information on the efficacy, feasibility, barriers and facilitators regarding the implementation of the intervention.

**Discussion:**

The APROPOS-II study introduces a locally tailored PCC-approach in six municipalities in the Netherlands that will contribute to the body of evidence regarding the effectiveness of PCC and its implementation. If this intervention has a positive effect on lifestyle behaviour changes, leading to improved pregnancy outcomes and the future health of prospective parents and their offspring, it could subsequently be upscaled to (inter)national implementation.

**Trial registration:**

Dutch Trial register: NL7784 (Registered June 6th, 2019).

## Background

Despite major advances in clinical research and medical technology, the prevalence of adverse maternal and neonatal health outcomes, such as pre-eclampsia and preterm birth, have only moderately decreased over the past decade [1]. As the first few weeks of pregnancy are crucial for gametogenesis, organogenesis and placental development, there is growing evidence that exposure to unhealthy lifestyle behaviours before or during pregnancy (such as alcohol consumption, smoking, physical inactivity, excessive weight gain, obesity and poor nutrition), often affect the future health of mothers, their offspring and future generations [2–4]. In the Netherlands, 85% of all pregnancies are planned pregnancies [5]. However, planning a pregnancy is not always accompanied by appropriate preparation for pregnancy. As such, only half of all pregnant women use folic acid in the correct dose for the correct amount of time and more than 60% of all women with a wish to conceive still use alcohol [5]. A recent study among future fathers showed that the majority of them took no action to improve their lifestyle behaviours before conception [6]. Therefore, it is important to improve awareness among prospective parents regarding (unhealthy) preconceptional lifestyle behaviours and its effect on reproductive outcomes and to encourage prospective parents to actively prepare for pregnancy.

One way to actively prepare for pregnancy is by using preconception care (PCC). PCC is defined as “a set of interventions that aim to identify and modify medical, behavioural and social risks to a woman’s health or pregnancy outcome through prevention and management” [7]. Despite a growing body of evidence showing that PCC can increase the health and well-being of prospective parents, the uptake of PCC-consults remains remarkably low [8]. Even more cause for concern is that vulnerable women, who often have multiple unhealthy lifestyle behaviours, are specifically hard to reach [9]. Previous studies have shown that barriers for the use of PCC are determined by the presence of preconditions, women’s beliefs, perceptions and experiences, given the limited availability and the inadequate infrastructure in which PCC is provided [10, 11]. Previously developed PCC-interventions tend to be clinical and focus on individual-level behaviour change (i.e. counselling women not to engage in risky behaviours) rather than examining social, structural and environmental factors that shape preconception health [12].

A previous feasibility study performed by our group (APROPOS) in one municipality of the Netherlands showed that a locally tailored PCC-approach has the potential to positively affect preconceptional lifestyle behaviours and increases the use of PCC among prospective parents [13]. After being exposed to the intervention, women were more likely to make at least one preconceptional lifestyle behaviour change compared to women who were not exposed to the intervention (adjusted OR 1.56 (95%CI 1.02–2.39)) [13]. However, before this locally tailored intervention can be implemented on an (inter)national level, the feasibility and effectiveness of this intervention needs to be analysed in a larger-scale implementation study. Therefore, we designed a second study (APROPOS-II) with implementation in more municipalities, a larger group of respondents, randomization, and assessment of a more comprehensive set of (clinical) outcomes.

### Aims and objectives

The aim of this study is to assess the effectiveness and the implementation process of a local PCC-approach (i.e. the intervention) on preconceptional lifestyle behaviours, health outcomes and the reach of PCC among prospective parents and healthcare providers. Therefore, we have specified the following objectives:
To determine the effect of the intervention on preconceptional lifestyle behaviours (e.g. smoking, alcohol use, folic acid use, physical activity) and other risk factors (e.g. body mass index, psychological distress, chronic illness) among women who recently conceived;to assess the effect of the intervention on the reach of prospective parents regarding PCC, the uptake of PCC and pregnancy preparation;to evaluate the implementation process in order to gain information on the feasibility, barriers and facilitators for the implementation of the local PCC-approach;to evaluate the sustainability of the intervention, with a specific focus on the diversity within and between the participating municipalities.

## Methods / design

### Study design

The APROPOS-II study uses a hybrid effectiveness-implementation design [14, 15]. In a stepped-wedge cluster-randomized controlled trial (RCT) we will implement and evaluate the effectiveness of the intervention. Randomization occurs at a cluster-level instead of an individual-level because the intervention has a community-approach in which the entire target population will be exposed to the intervention. All participating municipalities start with a control-phase, which will last 6–16 months depending on randomization order. The total duration of the study is 30 months (Fig. 1). The RE-AIM (reach, effectiveness, adoption, implementation, maintenance) framework will be used to evaluate the intervention and the implementation strategy [16].

**Fig. 1 Fig1:**
[figure not shown]
Timeline of the APROPOS-II study. All participating municipalities start with a control-phase, which will last 6–16 months depending on randomization order. After the control phase, the intervention will be implemented stepwise in every municipality

### Study population and setting

The study will be conducted in six municipalities distributed throughout the Netherlands (i.e. Amersfoort, Barneveld, Deventer, Tilburg, Utrecht and Zoetermeer). In total, ten community midwifery practices in these municipalities participate in the study. Municipalities were selected for diversity regarding their size (varying from 57,000–211,000 inhabitants), population, health challenges and organization of care. All women above the age of 18 years who adequately master the Dutch, English, Polish or Turkish language are eligible to participate in this study. Men are recruited through their participating partners.

Our intervention targets all men and women in their reproductive life span. In all six participating municipalities together, this is approximately 270,000 people [17]. Figure 2 shows how the number of people in the target population results in the total number of respondents.

**Fig. 2 Fig2:**
[figure not shown]
Overview of the studypopulation of the APROPOS-II study. This figure shows how the number of people in the target population results in the total number of respondents for the APROPOS-II study. The intervention targets all men and women in their reproductive life span within a municipality. We aim to include 2267 women in the study

### Intervention

The intervention used in this study is a PCC-approach tailored to the needs of prospective parent(s) and healthcare providers in a local setting. This intervention has been developed based on pre-implementation research in the APROPOS feasibility study [13]. The intervention has a dual-track approach based on both the uptake and the provision of PCC.
Uptake of PCC: To improve preconceptional lifestyle behaviours and the uptake of PCC, a social marketing strategy, directed towards prospective parent(s), will be distributed in each participating municipality. This online and offline social marketing strategy aims to trigger prospective parents to actively prepare for pregnancy by directing them towards reliable PCC-information and promoting individual PCC-consults.Provision of PCC: To improve interdisciplinary collaboration among healthcare providers, a local care pathway will be developed and implemented in each participating municipality, including interdisciplinary arrangements for collaboration and referral between primary, secondary and tertiary care. Moreover, a working conference will be held among local healthcare providers of multidisciplinary backgrounds and a stakeholder coalition will be formed.

### Implementation of the intervention

Concerning the uptake of PCC, the social marketing strategy has been developed by a professional and experienced marketing agency. A social marketing strategy uses commercial marketing technologies to design programs that can influence the behaviour of the target audience in order to improve personal welfare and that of society [18]. The theoretical foundation for this social marketing strategy is based on research regarding the target population’s perception from biological-, emotional-, social- and cultural point of views and resulted in the concept of “Woke Women®”, with the single-minded proposition: “Wake up smart (future) Mama! Let’s make your baby strong”. The social marketing strategy uses different channels of communication, e.g. online marketing, traditional offline marketing channels, word-of-mouth marketing and social networks will be addressed to start a social movement. Its purpose is to use existing social networks to encourage women to motivate each other towards healthy behaviour. Examples of materials used in the social marketing strategy are shown in Fig. 3 and more information about the social marketing strategy can be found on www.wokewomen.nl (in Dutch).

**Fig. 3 Fig3:**
[figure not shown]
Sociale marketing strategy Woke Women®. Examples of the promotional material (visuals) of the social marketing strategy Woke Women® which has been specifically developed for this study

Regarding the provision of PCC, the working conference for the healthcare providers aims to educate them on preconceptional health and risk factors using the national Preconception Indication List (PIL), emphasizes the importance of facilitating PCC and is used to conduct a region-specific bottleneck analysis [5] [19]. Subsequently, a multidisciplinary group of healthcare providers will form a local stakeholder coalition. With the input of these stakeholders, the intervention will be tailored to the participating municipality prior to implementation by adapting the dissemination locations, the design of the intervention and the essential elements included in the intervention.

### Clinical parameters and outcomes

Study parameters will be assessed by a questionnaire distributed among prospective parent(s) by the participating community midwifery practices in the first trimester of pregnancy. The questionnaire is based on validated questionnaires such as WHO - Quality of life questionnaire, the London Measure of Unplanned Pregnancy (LMUP), a validated preconception tool (www.zwangerwijzer.nl) and the APROPOS feasibility study [20, 21]. The questionnaire contains five sections: pregnancy planning, pregnancy preparation, healthy lifestyle behaviours and risk factors, personal situation and the prospective father. There are two versions of the questionnaire, one pre-implementation and one post-implementation. The post-implementation questionnaire contains additional evaluation questions about participant’s experiences with the social marketing strategy. An overview of all the variables in the questionnaire is shown in Table 1. The questionnaire is available in Dutch, English, Polish and Turkish; languages that are mastered by the majority of the inhabitants of the participating municipalities. The questionnaire for prospective fathers is shorter compared to the questionnaire for pregnant women and solely focusses on lifestyle behaviours and health beliefs.

**Table 1 Tab1:** Definition of primary and secondary outcomes of the APROPOS-II study

	Variable	Definition*
Pregnancy preparation	Level of pregnancy planning	London Measure of Unplanned Pregnancies (LMUP) [21]
	PCC health seeking behaviour	Acquired PCC-information through the internet, books, journals, folders or family & friends.
	PCC-consult	A consultation provided by a healthcare provider.
Modifying lifestyle behaviours & risk factors	Fruit intake	≥ 2 pieces of fruit a day [22]
	Vegetable intake	≥ 200 g of vegetables a day [22]
	Caffeine intake	≤ 1 caffeine-containing beverage [22]
	Exercising	≥ 150 min per week moderate or heavy intensive exercise, spread over various days [23]
	Smoking	No smoking [5, 24]
	Alcohol intake	No alcohol intake [5, 24]
	Folic acid usage	≥400 microgram per day, 4 weeks preconceptionally until 10 weeks gestation [5, 24]
	Medication usage	Risk-free medication [5]
	Psychological distress	A stable emotional state [5]
	Vaccination status	Vaccination status should be discussed with special attention to rubella, measles and whooping cough. Based on individual assessment of antibody titres; (re)vaccinations can be considered [24]
	Working conditions	Avoid contact with harmful working conditions [5]
Prenatal outcomes	Miscarriage	Loss of pregnancy before 24 weeks [25].
	Gestational Diabetes (GDM)	Diagnosed by a 75-g oral glucose tolerance test (OGTT) as the presence of either a fasting glucose level of ≥7.0 mmol/L (126 mg/dl) or a glucose level of ≥7.8 mmol/L (140 mg/dl) after two hours [26, 27]
	Pregnancy-induced hypertension (PIH)	New onset of hypertension (≥ 140 mmHg systolic and/or ≥ 90 mmHg diastolic blood pressure) after 20 weeks gestation measured on at least two occasions four hours apart [28, 29]
	Pre-eclampsia (PE)	PIH accompanied by proteinuria (≥300 mg in 24 h) [29, 30]
	Spontaneous preterm birth	Delivery with spontaneous onset before 37 weeks of gestation [31].
	Referral to secondary care	If complications occur or threaten to occur, the midwife will refer the woman to the obstetrician who will take over the care for as long as deemed necessary [32].
Birth outcomes	Mode of delivery	Spontaneous vaginal delivery, assisted vaginal delivery, or caesarean section [33].
	Referral to secondary care	If complications occur or threaten to occur, the midwife will refer the woman to the obstetrician who will take over the care for as long as deemed necessary [32].
Neonatal outcomes	Small for gestational age (SGA)	Birth weight < 10th percentile, based on Dutch national reference curves adjusted for parity, gestational age, sex and ethnicity [34].
	Congenital anomalies	Structural-morphological, functional and/or biochemical-molecular defects present at birth [35].
	APGAR- score	A score is a sum of the values assigned to the infant at 1 and 5 min of life, with a score of 7 or more indicating that the baby is in good to excellent condition [36].

*******
*Definitions are based on Dutch standards*

The primary outcome of this study is change in lifestyle behaviours. This is a composite outcome of four modifiable lifestyle behaviours (healthier diet, folic acid use, quit drinking and quit smoking during the preconception period), expressed as the number of women who preconceptionally change at least one of these lifestyle behaviours from inadequate to adequate. The definitions of healthy lifestyle behaviour are based on Dutch guidelines and are provided in Table 1.

Secondary outcomes are pregnancy outcomes (e.g. miscarriage, preterm birth, gestational diabetes) and the uptake of PCC. The definitions of these pregnancy outcomes are given in Table 1 and will be collected from the participants’ medical records after obtaining additional informed consent. The uptake of PCC will be measured through a section in the questionnaire and by the records of the midwifery practices on PCC-consults.

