### Statistical analysis

Statistical analysis will be performed using multilevel logistic regression analysis to take into account the clustering of respondents within municipalities. Data will be analysed anonymously on two levels; the respondents’ level (before and after the intervention) and the municipal level (differences between municipalities). Baseline characteristics will be compared between the pre- and post-intervention group and compared in a baseline table. Chi-square analysis and ANCOVA will be used to study the effects of the intervention on the adverse pregnancy outcomes. Adjusted odds ratios will be calculated taking into account the potential confounders: age, educational level and parity. *P*-values < 0.05 are considered statistically significant.

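### Exposure is not tied to conception date: if questionnaire date decides pre or post, women booking soon after launch dilute the primary odds ratio

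*Protocol article*

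**What the plan says.** The Abstract says that questionnaire data are collected before and after the intervention is introduced in each municipality. Under Clinical parameters and outcomes, the instrument is a "questionnaire distributed among prospective parent(s) by the participating community midwifery practices in the first trimester of pregnancy", and "There are two versions of the questionnaire, one pre-implementation and one post-implementation".

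The same section defines the primary outcome as a composite "expressed as the number of women who preconceptionally change at least one of these lifestyle behaviours from inadequate to adequate". Table 1 defines adequate folic acid use as "≥400 microgram per day, 4 weeks preconceptionally until 10 weeks gestation", so at least one component must begin four weeks before conception.

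Under Statistical analysis, respondents are analysed before and after the intervention, and "Baseline characteristics will be compared between the pre- and post-intervention group". Study design gives a control phase of 6–16 months within a 30-month study, with stepwise introduction thereafter. The text nowhere says which date places a woman in the pre or post group, and it mentions no lag or transition period. The Discussion concedes that respondents are already pregnant while the intervention aims at the time before pregnancy. It treats this as a matter of recruitment and retrospective reporting, not of exposure coding.

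**The concern.** The outcome window closes before the questionnaire is handed out. A woman who books a few weeks after launch conceived before launch, so the intervention could not have changed her primary outcome. If she is counted as post-intervention because her questionnaire falls after launch, she contributes a control-condition outcome to the intervention group.

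The error runs in one direction, towards an odds ratio of 1. It matters more if calendar time is modelled. A stepped wedge then draws much of its information from comparing municipalities that have just crossed with those about to cross. If the lag is as long as a step, those two are equally unexposed.

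**Working it through.** **The plan's own figure.** The sample size section gives 2167 women, with 363 in each of 6 municipalities, for OR 1.5, alpha 0.05, power 80% and ICC 0.02. It states no control rate. Assume 40%: OR 1.5 then gives 50% under intervention, and the two-sided two-proportion formula gives 388 per group, or 776. With 6 steps, 7 periods and about 51.6 women per municipality-period, the standard stepped-wedge design effect is [1 + 0.02(7×51.6 − 1)] / [1 + 0.02(4×51.6 − 1)] × 3(0.98) / [2(6 − 1/6)] = (8.204/5.108) × 0.252 = 0.405. The total is 776 × 0.405 × 7 = 2200, close to 2167 (control rates of 40–50% give 2177–2200). This calculation contains no allowance for a lag.

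**Lag (assumed).** Take the questionnaire at 8–10 weeks' gestation, which is 6–8 weeks after conception.
- Women booking within 6–8 weeks of launch (about 1.4–1.8 months) conceived before it. Their whole preconception period was unexposed. Lower value used: 1.5 months.
- Adding the four weeks in the folic acid definition gives 10–12 weeks (about 2.3–2.8 months). Upper value used: 3 months. This counts women with a straddling window as unexposed.

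**Share affected.** Assume launches at months 6, 8, 10, 12, 14 and 16 and even recruitment to month 30. Post-phase municipality-months are 24 + 22 + 20 + 18 + 16 + 14 = 114.
- Lag 1.5: 6 × 1.5 / 114 = 7.9%.
- Lag 3: 6 × 3 / 114 = 15.8%, from 3/24 = 12.5% in the first municipality to 3/14 = 21.4% in the last.

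**Before-after model, no period term.** The contrast is essentially within municipality. With control length C and post length P, each municipality has weight proportional to C×P and keeps a fraction 1 − L/P of the effect. The overall retained fraction is 1 − L × ΣC / Σ(C×P), where ΣC = 66 and Σ(C×P) = 144 + 176 + 200 + 216 + 224 + 224 = 1184.
- Lag 1.5: 1 − 1.5×66/1184 = 0.916, and exp(0.916 × ln 1.5) = 1.45.
- Lag 3: 1 − 3×66/1184 = 0.833, and exp(0.833 × ln 1.5) = 1.40.

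Generalised least squares with a random municipality effect (ICC 0.02, N = 2167) gives the same odds ratios.

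**With calendar period added.** The same model with fixed period effects gives:

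| Lag (months) | Retained fraction | Expected OR |
|---|---|---|
| 1.5 | 0.61 | 1.28 |
| 2 | 0.48 | 1.22 |
| 2.5 | 0.39 | 1.17 |
| 3 | 0.31 | 1.13 |

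**Power at a 40% control rate, lag 3 months.**

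| Coding | No period term | Monthly period effects |
|---|---|---|
| By questionnaire date | 0.96 | 0.10 |
| Recoded by conception date | 0.996 | 0.59 |
| Lag women excluded | 0.99 | 0.37 |

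With no lag at all, power would be 0.99 and 0.59. The 0.59 reflects the monthly grid and uneven phases assumed here and is not a separate criticism.

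**Sensitivity to recruitment.** If recruitment ended at month 22, post-phase time would be 66 municipality-months. A 3-month lag would then affect 18/66 = 27% of post-phase women, with OR about 1.33 without a period term and 1.11 with one.

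**The case against.** The strongest reply is that the article never states the allocation rule. The existence of two questionnaire versions does not say who receives which. Fig. 1 is not shown and could mark a transition period, and the full protocol may define exposure. This stands as a limit on wording: allocation by phase at booking is an inference. It is nevertheless the natural reading, because the article describes data collection and analysis alike as before versus after introduction. The Fig. 1 caption mentions only a control phase followed by stepwise implementation.

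The recruitment assumption is also open. At 23 women per month, 363 women take 363/23 = 15.8 months, not 30. A different pattern could move the affected share either way.

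Three stronger readings are tempting and not supported.
- *A lag of about five months, which removes nearly the whole effect.* That needs a three-month preconception window, which the article does not define.
- *The primary analysis would be crippled as it stands.* The severe figures need a calendar-time term and two-month steps. Statistical analysis names clustering by municipality and adjustment for age, educational level and parity, but no period term.
- *Control time is contaminated by provider activities.* Among the intervention components, "a working conference will be held among local healthcare providers of multidisciplinary backgrounds and a stakeholder coalition will be formed", and under Implementation of the intervention, "the intervention will be tailored to the participating municipality prior to implementation". That places the tailoring before implementation. It does not place the conference or coalition in the control phase, and no effect on women's behaviour before launch is shown.

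**Conclusion.** The point holds in conditional form. The outcome window precedes the questionnaire, the contrast is pre versus post, and the text neither anchors exposure to conception nor states a lag. If questionnaire date decides the group, about 8–16% of post-phase women carry an outcome formed wholly or mostly before launch, and the primary odds ratio is biased towards 1.

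The bias is modest under the analysis as written (1.5 becomes 1.45–1.40). It is serious if calendar period is modelled (1.28–1.13). These sizes rest on an assumed lag of 1.5–3 months, even recruitment over 30 months and, for the second range, one municipality per two-month step. The upper end of the lag gives partly exposed women no effect at all, so it leans towards overstatement. The direction does not depend on these choices.

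**What to change.** Before analysis, state that exposure is determined by estimated conception date relative to the municipality's randomised launch date. A woman is in the intervention group if she conceived at least a prespecified interval after launch, for example the four weeks already in the folic acid definition. Otherwise she is a control. If the model contains calendar period, define it by conception date too.

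Recode women rather than discard them. With monthly period effects and a 3-month lag, recoding keeps power at 0.59, against 0.37 if they are dropped. Add a sensitivity analysis that excludes women whose preconception window straddles launch.

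The cost is a few lines of analysis text and one data item. Gestational age at the questionnaire must be captured for every respondent. The article describes medical-record collection for pregnancy outcomes under additional consent, so it is safer to record gestational age with the questionnaire itself. Women with a partly exposed window will still be coded by convention, and the plan should say so.

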### Sample size calculation

Based on the results from the APROPOS feasibility study, we anticipate on an odds ratio of 1.5 in lifestyle behaviour change during the preconception period (primary outcome). Based on the sample size estimation method of Hemming and Taljaard, with an alpha of 0.05, power of 80% and a low intraclass correlation Coefficient of 0.02, the sample size was calculated to be 363 participants per unit with 6 units (=municipalities; 2167 in total, 23 participants per month per municipality) [41]. Considering our inclusion criteria, almost all women who have their intake visit during the study period are eligible respondents. Based on previous experience, we expect that 50–60% of these women will fill out the questionnaire.

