Strengths of this stepped-wedge cluster RCT are the diversity of the population in the participating municipalities and the tailored intervention that complies with the heterogeneity of local settings. Moreover, the detailed questionnaire investigating respondents’ lifestyle behaviours, health beliefs and the extent of planning of the current pregnancy based on validated questionnaires can be considered a strength of this study. In addition, the innovative social marketing strategy, the extensive process evaluation and the involvement of the prospective father highlight different and often neglected aspects of PCC-research.

A potential limitation of this study is the occurrence of selection bias, as participants who have actively prepared for their pregnancy are probably more eager to share their experience. However, in our previous feasibility study, response rates were high and the population characteristics were similar before and after introduction of the intervention [13]. Another limitation is the selection strategy, as the respondents of this study are pregnant while the interventions focusses on the preconceptional period. Previous studies already showed that prospective parents are very difficult to identify and recruit, therefore almost all PCC related studies obtain information retrospectively [46]. Finally, active participation of the healthcare providers is crucial to make the local PCC-pathway a success. Fortunately, the healthcare providers involved in the local PCC-pathway are driven to improve the awareness of PCC in their municipality and will be equipped to provide adequate PCC. All community midwifery practices have already been recruited and municipal policy makers are involved throughout the entire project.

With this study, we expect to effectively implement and evaluate a locally tailored PCC-approach. If this intervention will show to improve lifestyle behaviours, leading to improved pregnancy outcomes and future health of prospective parents and their offspring, it may be upscaled to (inter)national implementation.

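### Miscarriage is observed only from first-trimester enrolment, but the stated analysis ignores gestational week at entry; separately, its definition overlaps spontaneous preterm birth

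*Protocol article*

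**What the plan says.** All of this is in the protocol article.

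- **Definitions (Clinical parameters and outcomes, Table 1).** Miscarriage is "Loss of pregnancy before 24 weeks", with no start of the at-risk period. Spontaneous preterm birth is "Delivery with spontaneous onset before 37 weeks of gestation", with no lower limit.
- **Entry.** The same section has the questionnaire handed out "by the participating community midwifery practices in the first trimester of pregnancy". The Sample size calculation section ties eligibility to the intake visit: "almost all women who have their intake visit during the study period are eligible respondents". It adds that "we expect that 50–60% of these women will fill out the questionnaire". Pregnancy outcomes come from participants' medical records after a further consent.
- **Analysis (Statistical analysis).** "Chi-square analysis and ANCOVA will be used to study the effects of the intervention on the adverse pregnancy outcomes". Adjusted odds ratios are also planned, with age, educational level and parity as the covariates. Gestational age at enrolment is not among them, and no time-to-event method is named.
- **Design (Study design).** Every municipality begins in the control phase and crosses over later.
- **Limitations (Discussion).** The article acknowledges that "the respondents of this study are pregnant while the interventions focusses on the preconceptional period". It raises this because information on the preconception period is collected retrospectively. Unobserved early losses are not mentioned.

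**The concern.** A pregnancy lost before intake cannot enter the data set, so miscarriage is left-truncated at enrolment. Early in pregnancy the weekly risk of loss is taken to fall with each week, so a woman who enters at 8 weeks has more of that risk ahead of her under observation than one who enters at 10 weeks. A comparison of proportions, or an odds ratio adjusted for age, education and parity, treats the two as alike.

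That does no harm to the phase contrast if entry week has the same distribution in both phases. There are two ways it might not:

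- The social marketing works by "directing them towards reliable PCC-information and promoting individual PCC-consults". Women who prepare more actively, or who already know a midwifery practice from a preconception consult, might also book earlier.
- Control time is early and intervention time late in every municipality, so any drift in booking week over the 30 months falls unevenly on the two phases.

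The article's closing argument for scaling up refers to improved pregnancy outcomes, so a false signal of harm in miscarriage, or a masked benefit, would matter to how the trial is read.

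The overlap between miscarriage and spontaneous preterm birth is a separate defect. It has nothing to do with booking week.

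**Working it through.** **Figures in the document.** The article gives no miscarriage rate, no booking gestation and no power statement for miscarriage, so there is no stated figure to reproduce. Everything below on size is illustration. The only document figure used is the total of 2167 women, halved to about 1083 per phase.

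**Formula.** With weekly loss risk h(w), the same in both phases (no true effect), the risk observed after entry at week e is

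R(e) = 1 − product over w = e to 23 of (1 − h(w)).

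The spurious odds ratio for entry at week a (intervention) against week b (control) is [R(a)/(1 − R(a))] / [R(b)/(1 − R(b))].

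**Assumed weekly risks (none from the documents).**

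- Curve A: 2.0%, 1.5%, 1.0%, 0.6%, 0.4% in weeks 8 to 12, then 0.1%.
- Low: 0.6% in weeks 8–9, 0.4% in weeks 10–11, 0.1% in weeks 12–23.
- Mid: 1.5%, 0.8%, 0.15% over the same bands.
- High: 2.5%, 1.2%, 0.2% over the same bands.

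Worked example, curve A: R(10) = 1 − 0.990 × 0.994 × 0.996 × 0.999^11 = 3.06%. Then R(9) = 1 − 0.985 × 0.9694 = 4.51%. The odds ratio is (0.0451/0.9549)/(0.0306/0.9694) = 1.50.

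| Curve | R(10) | R(9) | R(8) | OR, 9 vs 10 | OR, 8 vs 9 |
|---|---|---|---|---|---|
| A | 3.06% | 4.51% | 6.42% | 1.50 | 1.45 |
| Low | 1.98% | 2.57% | 3.15% | 1.30 | 1.23 |
| Mid | 3.35% | 4.80% | 6.23% | 1.45 | 1.32 |
| High | 4.70% | 7.09% | 9.41% | 1.55 | 1.36 |

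A one-week shift therefore gives a spurious odds ratio of 1.23 to 1.55. Multiplying all weekly risks by a common factor hardly moves the ratio, because the risks are small. The shape of the curve matters, which is why several shapes are shown.

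**Smaller shift.** If half the women enter a week earlier, the intervention-phase risk is the mean of two adjacent columns. Curve A, weeks 9 and 8: (4.51 + 6.42)/2 = 5.47%, odds ratio 1.22. On the low curve the same shift gives 1.12 (from week 9) to 1.15 (from week 10).

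**No shift.** The odds ratio is 1.0 on every curve. A shift to later entry reverses the direction: the one-week range becomes 1/1.55 = 0.65 to 1/1.23 = 0.81.

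**Chance of P < 0.05 with no true effect**, two-sided, 1083 women per phase, clustering ignored, entry at week 9 against week 10: 15%, 40% and 65% on the low, mid and high curves.

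**Overlap.** Set side by side, the two rows of Table 1 both admit a spontaneous delivery at, say, 22 weeks: it is before 24 weeks and before 37 weeks. This needs no assumed rate. How many women would be affected cannot be derived from the article.

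**The case against.** The strongest reply is that the harmful mechanism is not documented. No section reports booking week by phase or says that the intervention changes it. The intervention promotes information and consults before conception, which is not the same as earlier antenatal intake. This stands: the article does not support the inference that the trial will show more miscarriages under the intervention. It supports only the statement that the planned comparison has no protection if entry week shifts.

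A reader might also infer that miscarriage is to be compared only as a raw proportion. That is not so, since adjusted odds ratios are planned as well. Their covariates, however, do not include entry week.

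The sizes rest wholly on assumed curves. That stands too, and the range is wide: the low curve puts the chance of a false positive for a one-week shift at only 15%.

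On the overlap, Table 1 speaks of loss in one row and delivery in the other, and says its definitions follow Dutch standards with cited sources not available here. The two may be meant to be exclusive. The table as printed does not make them so, but double counting is possible rather than certain, and nothing suggests it would differ between phases.

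Finally, this is a condensed article and miscarriage is one of several secondary outcomes. Model detail may well be left to a fuller document. But the article names a method and a covariate set for these outcomes, and they do not fit an outcome seen only after variable entry. That is a stated choice, not an omission.

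**Conclusion.** The point holds in a conditional form. Left truncation follows directly from how women are enrolled, and the stated analysis does not account for gestational week at entry. Whether this biases the phase comparison depends on a difference in entry week that the documents neither state nor exclude. If there is none, there is no spurious effect. If women enter one week earlier in the intervention phase, the spurious odds ratio is roughly 1.2 to 1.55 towards harm under the assumed weekly risks; later entry would bias towards benefit.

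The definitional overlap holds as written and needs no assumption, but its size is unknown. It should not be read as adding to the entry-week bias, and neither issue touches the primary outcome. This is a worthwhile, inexpensive improvement to a secondary analysis and does not threaten the trial's main conclusion.

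**What to change.** 1. Label the outcome as loss between enrolment and 24 weeks.
2. Analyse it with delayed entry at gestational age on enrolment, in a weekly discrete-time logistic or a Cox model, accounting for municipality and calendar period. The Statistical analysis section names no calendar-period term, so it has to be specified here.
3. Report the distribution of gestational week at entry by phase, so that readers can see whether a shift occurred.
4. Define spontaneous preterm birth as spontaneous-onset delivery at 24+0 to 36+6 weeks among pregnancies ongoing at 24 weeks. This uses the table's own boundary.

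The cost is two definition lines and a secondary analysis that is somewhat harder to present than a chi-square table. It needs gestational age at enrolment from the records. Delayed entry also assumes that, given the covariates, entry week is unrelated to the risk of loss. If women at higher risk book earlier, some bias remains, which is a further reason to report entry week by phase.
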